However, no pilot randomized controlled trial (RCT) has yet investigated Lo-TENS for common multimorbidity in older adults, nor explored its mechanistic pathways through ANS and inflammatory/metabolic biomarkers. Low-frequency transcutaneous electrical nerve stimulation (Lo-TENS; ≤10 Hz) is a non-invasive, low-risk intervention that modulates ANS activity by stimulating peripheral nerves (14). Prior studies have shown that Lo-TENS reduces sympathetic tone (measured via plasma norepinephrine levels and HRV) and improves clinical outcomes in patients with single chronic conditions, such as EH and T2DM (15–17) For example, Stein et al. demonstrated that 2 Hz Lo-TENS robustly reduces sympathetic activity and increases parasympathetic tone in healthy adults (15), and subsequent studies have validated these effects in older adults with cardiovascular conditions (18, 19). A recent randomized trial in patients with type 2 diabetes further suggested that TENS may improve glycemic variability, although its effect on HbA1c remains inconclusive, warranting further mechanistic investigation (20).

A pilot RCT is critical for this research question to assess feasibility (e.g., recruitment, intervention adherence, attrition) and estimate effect sizes for a subsequent definitive trial (21). As an pilot RCT, this study first aims to assess the feasibility of Lo-TENS delivery in older adults with multimorbidity and estimate effect sizes for a subsequent definitive trial. Second, we examine the efficacy of Lo-TENS as an adjunct to routine clinical management for improving blood pressure, glycemic control, and lipid profiles in older adults with common multimorbidity (≥2 of EH, T2DM, hyperlipidemia). Third, we explore the underlying mechanisms of Lo-TENS by testing whether changes in ANS function (HRV, norepinephrine) and inflammatory/metabolic biomarkers (IL-6, adiponectin, FGF21) mediate its effects on clinical outcomes (22, 23).

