### Sample size calculation

2.5

Sample size calculation is based on the primary outcome of FBG, using G*Power 3.1 software. A 2 × 3 analysis of variance (ANOVA) was selected for sample size calculation due to its suitability for assessing group (Lo-TENS vs. sham) × time (baseline, post-intervention, 4-week follow-up) interactions for continuous primary outcomes; mixed-effects models will be used for secondary analyses to account for potential missing data, consistent with modern pilot trial statistical practices. Based on prior Lo-TENS studies in T2DM (*f* = 0.282, the most conservative effect size) (20), *α* = 0.05, power = 0.80, and a 20% attrition rate, a total sample size of 50 participants (25 per group) is required. This sample size is appropriate for a pilot RCT to estimate effect sizes and assess feasibility.

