### Statistical analysis

2.8

The data analysis will be conducted using the Statistical Package for Social Sciences (SPSS) version 26. To ensure the accuracy of the data entry, it will be performed by two independent researchers who will cross-verify the input data for consistency. The baseline characteristics will be assessed using appropriated statistical tests based on the data distribution: independent *t*-tests for normally distributed data, Mann–Whitney *U* tests for non-parametric data, and Chi-square tests for categorical variables.

If the parameters meet the criteria for normal distribution, a repeated-measures ANOVA will be used to examine group × time interactions for primary and secondary outcomes. To account for multiple comparisons across the three co-primary outcomes (office BP, FBG, LDL-C), a Bonferroni correction will be applied, setting the significance level at *p* < 0.0167. Any two of these outcomes reach significance will be considered positive. Secondary outcomes will be analyzed descriptively and inferentially without correction, given their exploratory nature. To test the mechanistic hypothesis that ANS modulation and inflammatory/metabolic biomarkers mediate Lo-TENS’s effects on primary outcomes, we will conduct bootstrapped mediation analysis (5,000 resamples) using the PROCESS macro for SPSS 26. For each primary outcome (SBP, FBG, LDL-C), we will test whether the effect of Lo-TENS is mediated by pre-specified mechanistic markers (HF-HRV, norepinephrine, IL-6, and adiponectin), with 95% confidence intervals used to determine significant mediation. The magnitude of the effects will be quantified using partial eta-squared (*η_p_*^2^), with thresholds of 0.01, 0.06, and 0.14 indicating small, medium, and large effect sizes, respectively.

Subsequently, all analyses will be reiterated after the exclusion of drop-outs to conduct a per-protocol analysis.

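### The only effect-size measure fixed in Section 2.8, uncorrected partial eta-squared, is biased upward by about 0.02 at this sample size, and its labels would call most null results small effects

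*Protocol article*

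**What the plan says.** The Introduction of the protocol article gives as part of the first aim to "estimate effect sizes for a subsequent definitive trial", and the Abstract says the same. Section 2.5 defends the sample size partly on that ground: "This sample size is appropriate for a pilot RCT to estimate effect sizes and assess feasibility". That section plans for "group (Lo-TENS vs. sham) × time (baseline, post-intervention, 4-week follow-up) interactions" and concludes that "a total sample size of 50 participants (25 per group) is required", at f = 0.282 with 20% attrition.

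Section 2.8 states that "a repeated-measures ANOVA will be used to examine group × time interactions for primary and secondary outcomes". On effect size it says: "The magnitude of the effects will be quantified using partial eta-squared", with "thresholds of 0.01, 0.06, and 0.14 indicating small, medium, and large effect sizes, respectively". No other effect-size measure is named. Success is defined separately, by p < 0.0167 on any two of the three co-primary outcomes.

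**The concern.** Sample partial eta-squared is a ratio of sums of squares. It is never negative, so chance differences between the arms can only push it up. In a trial of 40 to 50 people that push is large relative to the lowest cut-off of 0.01. A reader of the pilot report would then see the word *small* beside most outcomes even if Lo-TENS did nothing, and the values available to whoever plans the definitive trial would be too high on average.

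The index also suits the aim poorly for a second reason. For an interaction over three visits it has no sign, so benefit and harm get the same value. It has no units, so it gives no difference in mmHg or mmol/L. It also pools weeks 4 and 8, whereas the Abstract sets the co-primary outcomes at post-intervention.

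**Working it through.** **Inputs.** From Section 2.5: 2 groups, 3 visits, N = 50, 20% attrition (50 × 0.8 = 40 completers), f = 0.282. From Section 2.8: the group by time test, the three cut-offs and the 0.0167 level. Sphericity is assumed unless stated otherwise. I use both 40 and 50, because drop-outs are excluded only in the later per-protocol repeat.

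**The plan's own figure.** The article gives no figure for how partial eta-squared behaves under no effect, so there is none to reproduce on that point. The total of 50 depends on the correlation between visits, which is not given. With λ = f²·3N/(1 − ρ) and df 2 and 2(N − 2), 80% power at α = 0.05 needs 42 completers at ρ = 0 and 38 at ρ = 0.1. Dividing by 0.8 gives 53 and 48, so 50 fits ρ of about 0 to 0.1.

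**No effect.** The interaction has df 2 and 2(N − 2). Partial eta-squared = 2F/(2F + df2) then follows a Beta(1, N − 2) distribution, so

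P(value ≥ t) = (1 − t)^(N − 2), with mean 1/(N − 1).

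| | N = 40 | N = 50 |
|---|---|---|
| Mean | 1/39 = 0.026 | 1/49 = 0.020 |
| At least 0.01 | 0.99^38 = 68.3% | 0.99^48 = 61.7% |
| At least 0.06 | 0.94^38 = 9.5% | 0.94^48 = 5.1% |
| At least 0.14 | 0.86^38 = 0.3% | 0.86^48 = 0.07% |

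Two variations at N = 40: a single-df contrast of post-intervention with baseline gives 53.9% at least *small* and 12.8% at least *medium*. A strongly non-spherical covariance, simulated with 20,000 trials, gives about 59% at least *small*.

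**Significance.** Solving (1 − t)^38 = 0.0167 gives t = 1 − 0.0167^(1/38) = 0.102. With 40 completers, every value from 0.01 to about 0.10 is therefore labelled *small* or *medium* but is not significant.

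**Bias when there is an effect.** Means of simulated noncentral F draws, N = 40:

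| True value | Mean partial eta-squared | Mean epsilon-squared |
|---|---|---|
| 0 | 0.026 | 0.000 |
| 0.01 | 0.035 | 0.010 |
| 0.06 | 0.082 | 0.057 |
| 0.074 (f = 0.282) | 0.094 | 0.070 |
| 0.14 | 0.157 | 0.134 |

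The excess is 0.017 to 0.026. Epsilon-squared, a bias-corrected index, stays within about 0.006 of the true value.

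**If the observed value sized the next trial.** Required N varies roughly as 1/f², so the shortfall is 1 − (true f²)/(observed f²). The mean observed f² is (2 + λ)/(df2 − 2).

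- λ = f²·df2, N = 40: λ = 0.0795 × 76 = 6.04 and mean f² = 8.04/74 = 0.109 against 0.080. The shortfall is 27%. By the median (0.094) it is 15%.
- λ = f²·df2, N = 50: λ = 7.63 and mean f² = 9.63/94 = 0.102. The shortfall is 22%. By the median it is 12%.
- λ = f²·3N (ρ = 0), N = 40: λ = 9.54, mean f² = 11.54/74 = 0.156 against 9.54/76 = 0.126. The shortfall is about 20%. By the median it is 10%.
- λ = f²·3N (ρ = 0), N = 50: λ = 11.93, mean f² = 13.93/94 = 0.148 against 11.93/96 = 0.124. The shortfall is 16%. By the median it is 8%.

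The first form of λ gives 57% power with 40 completers at α = 0.05; the second gives 78%, closer to the planned 80%. The range is therefore about 8% to 27%.

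**The case against.** The strongest reply is that partial eta-squared with these cut-offs is a common convention, that the labels are adjectives placed beside a test, and that nothing in the protocol turns on them. Much of this stands:

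- The bias belongs to the uncorrected estimator. It would be the same with other cut-offs or with none, so a reader who infers that the grading inflates the effect sizes goes too far.
- Success rests on p < 0.0167, which at N = 40 needs ten times the *small* cut-off. A label of *small* is not a claim that the treatment works.
- Under no effect the labels are almost all *small*; *medium* is uncommon and *large* very rare.
- A reader might infer that the definitive trial will be sized on the observed partial eta-squared. The protocol does not say so. Section 3.1 says only that the findings will inform a fully powered trial, and Section 3.4 concedes that 50 participants limit the efficacy findings.
- The higher shortfall figures use a mean and a noncentrality that does not match the planned power. In the 27% case only about 58% of pilots would overestimate at all.
- Intervals, standard deviations and visit correlations may be specified in a fuller plan, so their absence from the article is not the fault.

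What does not fall is the mismatch between a stated measure and a stated aim. The article commits to this one index, says effect sizes are to be estimated for later use, and itself sizes the pilot from a Cohen's f, which converts directly to and from partial eta-squared.

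**Conclusion.** The concern holds in a limited form. Section 2.8 fixes an upward-biased, unsigned and unit-free index as the only effect-size measure for a pilot that aims to estimate effect sizes. The bias is about 0.02 at 40 to 50 participants. Under no effect and sphericity, 68% of outcomes (62% with 50 analysed) would be labelled at least *small*.

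This does not make the trial's success rule wrong, and the conventional cut-offs are not an error in themselves. The 8% to 27% shortfall is conditional: it assumes that the next trial is sized on the observed value and that the true effect is f = 0.282, and it varies with the number analysed, the noncentrality assumed and the use of mean or median. The matter is worth correcting before analysis but does not threaten the trial's validity.

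**What to change.** In Section 2.8, name the between-group mean difference with its 95% confidence interval as the effect-size estimate for each co-primary outcome, in mmHg for office SBP and mmol/L for FBG and LDL-C. If a standardised index is also wanted, use a bias-corrected one (omega-squared or epsilon-squared for the interaction, or Hedges' g for the week-4 contrast), give its confidence interval, and drop the small, medium and large labels.

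The cost is wording only, with no change to recruitment, visits or data collection. Reported effects will look slightly less favourable.

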### Ethical considerations

2.9

The study protocol is approved by the Ethics Committee of The Second People’s Hospital of Kunming (approval number: 202401011). All participants provide written informed consent. Adverse events (e.g., skin irritation, dizziness) are monitored throughout the study; any serious adverse events are reported to the Ethics Committee and Safety Supervision Committee within 24 h. A Safety Supervision Committee (independent of the study team) oversees participant safety and data integrity. Participants may withdraw from the study at any time without penalty.

## Discussion

3

### Expected findings

3.1

This pilot RCT is the first to investigate Lo-TENS as an adjunctive therapy for common multimorbidity in older adults, with a focus on feasibility, efficacy, and mechanisms. We hypothesize that Lo-TENS will be feasible (high recruitment/adherence rates, low attrition/adverse event rates) and effective in reducing SBP, FBG, and LDL-C compared to sham stimulation. We also expect that Lo-TENS will improve ANS function (increased HF-HRV, reduced NE) and modulate inflammatory/metabolic biomarkers (reduced IL-6, increased adiponectin/FGF21), with these markers mediating the intervention’s effects on primary outcomes (5, 22). These findings will provide critical data to inform a fully powered definitive RCT, which is necessary to confirm Lo-TENS’s efficacy and translate it into clinical practice.

### Mechanistic implications

3.2

The study’s mechanistic focus addresses a key gap in current Lo-TENS research: while prior studies have shown Lo-TENS improves clinical outcomes in single chronic conditions, the pathways linking Lo-TENS to multimorbidity improvement remain unclear (16, 17, 20). By testing mediation by ANS and inflammatory/metabolic markers, we aim to validate the hypothesis that sympathetic over-activation is a unifying target for multimorbidity management (8, 12). If confirmed, this mechanism would support the use of Lo-TENS as a “disease-modifying” adjunctive therapy, rather than just a symptomatic treatment—potentially transforming multimorbidity care in older adults.

### Translational potential

3.3

Lo-TENS has significant translational potential due to its low cost, non-invasiveness, and ease of administration. If Lo-TENS is found to be feasible and effective in this hospital-based pilot trial, future research will focus on adapting the intervention for community-based self-administration—a critical step for translation to real-world geriatric care (32). This will include evaluating low-cost home Lo-TENS devices, developing caregiver/patient training materials, and testing remote monitoring strategies to ensure consistent stimulation delivery in non-clinical settings. Given Lo-TENS’s low cost and minimal side effects, it has significant potential to reduce polypharmacy burden and improve multimorbidity management in underserved geriatric populations worldwide (6, 7). Additionally, the feasibility data from this pilot will inform the design of larger, multi-center trials to confirm efficacy in diverse older adult populations.

### Limitations

3.4

This pilot RCT has several limitations that should be acknowledged. First, the small sample size (50 participants) limits the generalizability of efficacy findings; however, this is appropriate for a pilot trial focused on feasibility and effect size estimation (21). Second, the single-center design may limit external validity; future multi-center trials should include diverse clinical settings (e.g., urban/rural hospitals, community health centers) to improve generalizability. Third, the single-blinded design (therapists not blinded) may introduce performance bias; however, we minimized this by ensuring outcome assessors and data analysts are blinded, and we will quantify unblinding bias using a post-intervention survey (30). Fourth, a further limitation is the potential for attrition related to geriatric-specific factors (e.g., mobility limitations, frailty, or polypharmacy-related fatigue), which may impact follow-up completion. To mitigate this, we have implemented flexible intervention scheduling and telephone reminders for follow-up assessments; attrition rates and reasons for dropout will be reported in detail to inform feasibility for future community-based trials. Finally, the 4-week intervention period and 4-week follow-up are short; longer-term trials are needed to assess the sustainability of Lo-TENS’s effects.

### Future directions

3.5

Based on the pilot’s findings, future research will focus on three key areas: (1) Conducting a fully powered, multi-center RCT to confirm Lo-TENS’s efficacy for multimorbidity in older adults, with a longer intervention/follow-up period (e.g., 12 weeks); (2) Exploring subgroup analyses (e.g., age, number of comorbidities, frailty status) to identify which older adults benefit most from Lo-TENS; (3) Developing and testing a community-based Lo-TENS intervention (self-administered by patients/caregivers) to improve accessibility and scalability (32, 33). Additionally, future studies could explore combining Lo-TENS with other non-pharmacological interventions (e.g., exercise, dietary counseling) to maximize clinical benefits for older adults with multimorbidity.

## Glossary

ANS: Autonomic Nervous System
ABPM: 24-Hour Ambulatory Blood Pressure Monitoring
CRP: C-Reactive Protein
EH: Essential Hypertension
ELISA: Enzyme-Linked Immunosorbent Assay
FBG: Fasting Blood Glucose
FGF21: Fibroblast Growth Factor 21
HF-HRV: High-Frequency Heart Rate Variability
IL-6: Interleukin-6
ITT: Intention-to-Treat
LDL: Low-density lipoprotein
LDL-C: Low-Density Lipoprotein Cholesterol
LF-HRV: Low-Frequency Heart Rate Variability
Lo-TENS: Low-Frequency Transcutaneous Electrical Nerve Stimulation
NE: Norepinephrine
PP: Per-Protocol
RCT: Randomized Controlled Trial
SBP: Systolic Blood Pressure
SF-36: 36-Item Short Form Health Survey
T2DM: Type 2 Diabetes Mellitus
